### Secondary outcome measurements

Secondary outcomes include the mean changes in the WOMAC subscales (pain, stiffness, and function) at 5 and 13 weeks from baseline. As such, we will investigate which subscales affect the global scale value of the WOMAC, which is the primary outcome measurement.

Health-related quality of life (HRQL) will be assessed by the Short-Form 36v2 Health Survey (SF-36) at 5 and 13 weeks from baseline. The SF-36 is used to measure the general health status and quality of life of patients and non-patients. It comprises a total of 36 questions in 8 categories, and higher scores indicate a better level of function. Han *et al.* developed a Korean version of the SF-36 and assessed its reliability and validity for use in health-related quality of life measurements for elderly Korean patients [29].

Depression will be assessed by a mean change in Beck Depression Inventory (BDI) scores at 5 and 13 weeks from baseline. The BDI, developed by Beck AT in 1967, is a 21-question multiple-choice questionnaire that is one of the most widely used scales for measuring the severity of depression. It is composed of items related to the depression symptoms of hopelessness and irritability, cognition (such as guilt and feelings of being punished), and physical symptoms (such as fatigue and weight loss); higher total scores indicate more severe depressive symptoms [30].

To assess physical activity, a physical performance test will be performed at 5 and 13 weeks from baseline. The physical performance test is composed of the timed stand, standing balance, and 6-minute walk tests. 1) The timed stand test evaluates lower extremity muscle power by measuring the time required to complete 10 full stands from a sitting position. 2) The standing balance test assesses balance in particular positions, such as tandem, semi-tandem, side-by side, and one-legged stands. 3) The 6-minute walk test measures the distance walked at the greatest speed possible within 6 minutes to assess the functional exercise capacity of patients [31].

Global knee pain will be assessed using the patient global assessment and numerical rating scale (NRS). The patient global assessment score is a self-reported 5-point

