measurement used to evaluate overall improvement after treatment. Participants individually evaluate their improvement from baseline by selecting one of 5 options (much improved, minimally improved, no change, minimally worse, or much worse) at 5 and 13 weeks from baseline. The pain NRS (0 = no pain and 10 = worst possible pain) is a standard instrument in chronic pain studies that is used to measure pain intensity [32]. We will evaluate the mean change in the NRS within 7 days of the study visits at 5 and 13 weeks from baseline.

The treatment expectancy of participants will be evaluated by the Treatment Expectancy Questionnaire (1 = not at all, 5 = somewhat and 9 = very much), which has been transformed and translated into Korean from the "Credibility and Expectancy Questionnaire" [33]. Participants will be asked "How much do you feel moxibustion therapy will help to reduce your symptoms?" at the first visit.

A blood sample will be obtained at baseline and 5 weeks from baseline to measure the C-reactive protein (CRP) levels and the erythrocyte sedimentation rate (ESR). We will therefore evaluate inflammation and tissue damage after moxibustion treatment. The detailed outcome measurement time points are provided in Table 1.

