| Patient Global Assessment          |        |   | • |   |   |   |   |   |   |   |    |    |    |    | •  | •  |
| Safety Assessment                  |        |   | • | ○ | ○ | ○ | ○ | ○ | ○ | ○ | ○  | ○  | ○  | ○  | •  | •  |

S: Screening Period, T: Treatment Period, F: Follow-up Period, K-WOMAC: Korean Western Ontario and McMaster Osteoarthritis Index, •: Both the moxibustion group and the usual care group, ○: Only the moxibustion group.

continuous data and a chi-squared test or Fisher's exact test for categorical data, according to whether the data are normally distributed. An analysis of covariance (ANCOVA) will be performed for the primary endpoint (global scale value of WOMAC) and secondary endpoints (WOMAC subscales (pain, stiffness, and function), HRQL, depression, physical activity, and patient global assessment) at 5 weeks and 13 weeks from baseline. The ANCOVA model will include group as a fixed effect and baseline measurements and centres as covariates. The mean difference from baseline values to the end of treatment in each group will be examined using a paired *t*-test or a Wilcoxon signed rank test. To identify a trend, we will also perform a repeated measures analysis of variance.

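### The Patient Global Assessment already rates change since baseline, yet the plan records it at baseline, adjusts for baseline and tests its difference from baseline

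*Protocol*

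**What the plan says.** **Definition.** Under Secondary outcome measurements, the scale is a "measurement used to evaluate overall improvement after treatment". The task is set out as follows: "Participants individually evaluate their improvement from baseline by selecting one of 5 options (much improved, minimally improved, no change, minimally worse, or much worse". The same sentence gives the timing as weeks 5 and 13 and mentions no baseline rating.

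**Schedule.** In Table 1, the row "Patient Global Assessment" is marked for both groups at visits 2, 14 and 15 (weeks 1, 5 and 13). Visit 2 is the baseline visit: under Primary outcome measurement, K-WOMAC is taken there before moxibustion starts.

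**Analysis.** The Statistical analysis section assigns ANCOVA to the primary endpoint and to a list of secondary endpoints that ends "HRQL, depression, physical activity, and patient global assessment) at 5 weeks and 13 weeks from baseline". One model serves them all: "The ANCOVA model will include group as a fixed effect and baseline measurements and centres as covariates". The within-group analysis follows: "The mean difference from baseline values to the end of treatment in each group will be examined using a paired" *t*-test or a signed rank alternative. It names no endpoint and exempts none. The same section replaces missing data by last observation carried forward (LOCF), again without exception.

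**The concern.** A scale such as K-WOMAC measures a state. It has a value before treatment and a value after, and the analyst can adjust for the first or subtract it. The Patient Global Assessment measures a transition: the participant makes the comparison with baseline, and the answer is the change. Before treatment there is nothing to compare, so a rating taken at visit 2 is not a baseline value in the sense the model needs.

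The plan nevertheless treats this scale like the state scales in three places: the schedule, the ANCOVA covariate and the paired test. LOCF creates a fourth risk, because a visit-2 entry on file could be carried into week 5 as if it were a judgement on treatment. At stake is the interpretation of the participants' own verdict on overall improvement, not the primary result.

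**Working it through.** **Text against table.** Secondary outcome measurements gives weeks 5 and 13. Table 1 gives visit 2 as well. Both cannot be right, and the definition of the scale fits only the text.

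**The covariate.** The ANCOVA sentence says baseline measurements. For one model applied to many endpoints, the natural reading is each endpoint's own baseline. There are two cases.

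- *Everyone answers logically.* At baseline the only logical answer is *no change*, which is a constant. The design matrix for 212 participants has an intercept, group, three indicators for the four centres, and the constant covariate: 1 + 1 + 3 + 1 = 6 columns. Its computed rank is 5, because the constant column is a multiple of the intercept. The covariate's coefficient cannot be estimated, the term drops out, and the model reduces to group and centre. The group contrast is still estimated.
- *Answers vary.* They are then not ratings of change since baseline as the Protocol defines them. Under Randomisation and allocation concealment, envelopes are opened only after all baseline assessments, so the covariate precedes allocation. It does not bias the group contrast and costs one degree of freedom, but the adjustment has no defined meaning.

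**The paired test.** Let *Y* be the week-5 rating, on any numeric coding (the Protocol gives none), and *B* the visit-2 entry. The test uses *Y* − *B*. If *B* is the code for *no change*, this only shifts *Y* by a constant and asks whether the average rating differs from *no change*. If *B* varies, a meaningless quantity is subtracted from a score that is already a change.

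**Possible reach of LOCF.** The inputs come from the Sample size section: 212 participants and 20% dropout. The Protocol gives no figure for this scale. Its own sample size reproduces: 2 × (15.4 × (1.960 + 0.842) / 6.65)² = 84.19 per group, against its approximate 84. Then 84.19 / 0.80 = 105.2, rounded up to 106, and 2 × 106 = 212.

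- Upper bound: 0.20 × 212 = 42.4, about 42 week-5 ratings. This needs all dropout to fall before week 5, a recorded visit-2 entry, and LOCF applied to that entry.
- Lower bound: 0. If the text governs and no visit-2 rating exists, there is nothing to carry to week 5.
- A participant rated at week 5 but missing at week 13 is not part of this problem, because the value carried is a real post-treatment rating.

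**The case against.** The strongest reply is that little harm reaches the treatment comparison, and much of that reply stands.

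- A reader might infer that the stated model cannot be fitted. The documents do not support this. Only the constant covariate's coefficient is lost; the group contrast survives, and it is not biased by a covariate taken before allocation.
- A reader might infer that 42 ratings would be invented. The 20% is a sample-size allowance with no time point attached, follow-up runs to week 13, and the Protocol does not say whether baseline values are carried forward. The figure is only a conditional upper bound. Carrying a baseline value forward also imputes zero change on the other scales, so part of this is a general weakness of LOCF.
- The words baseline measurements need not mean the scale's own baseline. That reading is an inference, though the natural one.
- With about 106 per arm, a linear model on a five-level score gives usable large-sample inference on a mean difference. Nothing in the documents says that the steps between categories are unequal, so a claim that ANCOVA is invalid for that reason would go too far.
- A separate statistical analysis plan may name another method.

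The reply does not remove the mismatch between definition, schedule and analysis. The Protocol itself fixes all three, and collecting the visit-2 rating is a matter for the Protocol whatever a later plan says.

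**Conclusion.** The point holds in limited form. As defined, the Patient Global Assessment has no meaningful baseline value. Table 1 contradicts the text by scheduling one, and the stated analysis uses it as a covariate and as a subtrahend. The baseline adjustment is therefore empty or adjusts for noise, and the paired test does not fit the outcome. The group contrast remains estimable and unbiased by this covariate. Between 0 and about 42 of 212 week-5 ratings could be replaced by a pre-treatment answer, depending on dropout timing and on how LOCF is applied.

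This rests on two assumptions: that baseline measurements means each endpoint's own baseline, and that visit-2 ratings precede allocation as the randomisation text says. Table 1 places the allocation mark at visit 1, so the second assumption relies on the text. The outcome is secondary, and the primary analysis and sample size are untouched. The correction is still worth making because it is specific and nearly free.

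**What to change.** 1. In Table 1, delete the visit-2 mark for the Patient Global Assessment, so that the schedule agrees with Secondary outcome measurements.
2. In Statistical analysis, take this scale out of the own-baseline ANCOVA and exempt it from the paired test against baseline.
3. State that no visit-2 value of this scale is carried forward.
4. Compare groups at weeks 5 and 13 with an ordinal method: either a proportional-odds model with group, centre and baseline K-WOMAC (already collected at visit 2), or a van Elteren test stratified by centre.
5. Report the percentage improved (the two improved categories combined) in each group, with a confidence interval for the comparison.

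The cost is a few sentences of rewording and one questionnaire fewer at visit 2. The proportional-odds model brings its own assumption of a common odds ratio across categories; the van Elteren test does not need that model but gives no adjusted effect estimate. Sample size and the primary analysis do not change.

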#### Additional analyses

##### Economic evaluation

The economic evaluation will be conducted from a social perspective, and all costs and consequences of the competing interventions will be considered regardless of who pays for or benefits from them. All cost data will be collected through a cost questionnaire that participants

will complete at 5 weeks and 13 weeks after baseline. Researchers will explain these to all of the participants, and obtain the consent before collecting economic data. The costs considered in the present analysis will include the direct healthcare-related costs of moxibustion treatment, physician visits, hospital stays (without consideration of private billings), and any drugs (including patient co-payments). In addition to health insurance costs, the indirect costs caused by lost workdays will also be taken into account. Health utility will be measured in quality-adjusted life years calculated for each patient using the SF-36 at 5 weeks and 13 weeks after baseline, and the K-WOMAC pain subscale will also be used to analyse cost-effectiveness. The cost-utility and cost-effectiveness analyses will be performed through a decision analysis. The analysis period will be 5 weeks, and the trend will also be evaluated at 13 weeks.

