### Design and setting

This is a multicentre, pragmatic, randomised, assessor-blinded, controlled, parallel-group study. From May 2011 to November 2011, 4 clinical research centres in Korea will participate in this trial: the Korea Institute of Oriental Medicine (Daejeon University Hospital) in Daejeon, Gachon University Gil Oriental Medical Hospital in Incheon, Dongshin University Gwangju Oriental Hospital in Gwangju, and Semyung University Oriental Medicine Hospital in Jecheon. The population of each city is greater than 140,000, and the estimated prevalence rates of KOA are 14.9% over 40 years old [22] and 38.1% over 65 years old [23] in Korea. Recruitment will therefore be expected to be completed within the study period. To recruit the participants, we will advertise in the media (daily papers, local newspapers, and public newsletters), in each hospital, and on the internet homepages of hospitals and public institutions. Eligible participants will be randomly allocated into 2 groups (the moxibustion group or the usual care group) with a 1:1 allocation ratio and receive treatment for 4 weeks with 2 months of follow-up (Figure 1). The evaluation of participants and the analysis of the results will be

[figure not shown]

performed by professionals blinded to the group allocation. Written consent will be obtained from each participant before the start of this trial. We will obtain oral and written consent from each participant before collecting information at the first visit.

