**Table 1 Schedule for treatment and outcome measurements**

|                                    | Period | S |   |   |   |   |   |   | T |   |    |    |    |    |    | F  |
|------------------------------------|--------|---|---|---|---|---|---|---|---|---|----|----|----|----|----|----|
|                                    | Visit  | 1 | 2 | 3 | 4 | 5 | 6 | 7 | 8 | 9 | 10 | 11 | 12 | 13 | 14 | 15 |
|                                    | Week   | 1 | 1 | 1 | 1 | 2 | 2 | 2 | 3 | 3 | 3  | 4  | 4  | 4  | 5  | 13 |
| Informed Consent                   |        | • |   |   |   |   |   |   |   |   |    |    |    |    |    |    |
| Demographic Characteristics        |        | • |   |   |   |   |   |   |   |   |    |    |    |    |    |    |
| Medical History                    |        | • |   |   |   |   |   |   |   |   |    |    |    |    |    |    |
| Knee X-Ray                         |        | • |   |   |   |   |   |   |   |   |    |    |    |    |    |    |
| Inclusion/Exclusion Criteria       |        | • |   |   |   |   |   |   |   |   |    |    |    |    |    |    |
| Conformity Assessment              |        | • |   |   |   |   |   |   |   |   |    |    |    |    |    |    |
| Treatment Expectancy Questionnaire |        | • |   |   |   |   |   |   |   |   |    |    |    |    |    |    |
| Blood Test                         |        | • |   |   |   |   |   |   |   |   |    |    |    |    | •  |    |
| Vital Signs                        |        | • | • | ○ | ○ | ○ | ○ | ○ | ○ | ○ | ○  | ○  | ○  | ○  | •  | •  |
| Change in Medical History          |        |   | • | ○ | ○ | ○ | ○ | ○ | ○ | ○ | ○  | ○  | ○  | ○  | •  | •  |
| Random Allocation                  |        | • |   |   |   |   |   |   |   |   |    |    |    |    |    |    |
| Moxibustion Treatment              |        |   | ○ | ○ | ○ | ○ | ○ | ○ | ○ | ○ | ○  | ○  | ○  | ○  |    |    |
| K-WOMAC                            |        |   | • |   |   |   |   |   |   |   |    |    |    |    | •  | •  |
| Beck Depression Inventory          |        |   | • |   |   |   |   |   |   |   |    |    |    |    | •  | •  |
| The Short-Form 36v2 Health Survey  |        |   | • |   |   |   |   |   |   |   |    |    |    |    | •  | •  |
| Pain Numerical Rating Scale        |        | • | • |   |   |   |   |   |   |   |    |    |    |    | •  | •  |
| Physical Function Test             |        |   | • |   |   |   |   |   |   |   |    |    |    |    | •  | •  |

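### Costs are collected only at weeks 5 and 13, so the incremental cost cannot be adjusted for resource use before entry; this loses precision but does not bias the comparison

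*Protocol*

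**What the plan says.** The Objective section names cost-effectiveness and cost-utility within the second aim. Under Economic evaluation the protocol gives one source of cost data: "All cost data will be collected through a cost questionnaire", which participants "will complete at 5 weeks and 13 weeks after baseline". The costs counted are moxibustion, physician visits, hospital stays, drugs and lost workdays. The analysis period is 5 weeks, with the trend examined at 13 weeks, and the method is a decision analysis. No administration at baseline is mentioned.

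On consent, the same section says: "Researchers will explain these to all of the participants, and obtain the consent before collecting economic data". It names no visit.

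The Secondary outcome measurements section closes with "The detailed outcome measurement time points are provided in Table 1". Table 1 has a visit-2 entry for K-WOMAC, SF-36, BDI, the pain scale and the function tests, and repeats them at visits 14 and 15 (weeks 5 and 13) in both groups. It has no row for the cost questionnaire.

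**The concern.** The two effect measures in the economic evaluation, the SF-36 and the K-WOMAC pain subscale, both have a measurement before treatment. The cost side has none.

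Participants can enter already using drugs, physical treatment or physician visits, and with different amounts of lost work. The exclusion criteria remove recent acupuncture, moxibustion, cupping, herbal medicine and certain joint injections, but not these other sources of cost. Both groups may use any treatment during the trial, so habits formed before entry can carry on into follow-up costs and add variation between participants. A baseline cost would explain part of that variation.

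Nothing else in the protocol supplies it. The Usual care section asks participants to report only treatments that are new after entry, and the medical history at visit 1 yields neither costs nor workdays. An analysis plan cannot repair this later, because the covariate would have to be collected before allocation.

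**Working it through.** **Is there a figure to reproduce?** The protocol gives no figure for costs: no SD, no correlation and no expected completion rate. The only number carried over is the group size, which is planned for the WOMAC. It reproduces: n = 2 × (1.96 + 0.8416)² × (15.4/6.65)² = 84.2 per group, against the stated 84 or so; 84.2/0.80 = 105.2, rounded up to 106. An exact t-test calculation gives 85.2 before dropout. This point does not change that calculation.

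**Size of a chance imbalance in baseline cost.** In units of the baseline cost SD, the standard error of the difference between arms is sqrt(2/n).
- n = 106: sqrt(2/106) = 0.137 SD.
- n = 106 × 0.80 = 84.8, after the 20% dropout the protocol assumes: sqrt(2/84.8) = 0.154 SD.

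**How much of it reaches the incremental cost.** With equal SDs at baseline and follow-up, the expected carry-over is the correlation rho times the imbalance. For a one-standard-error imbalance at n = 106:
- rho = 0.3: 0.3 × 0.137 = 0.04 SD.
- rho = 0.6: 0.6 × 0.137 = 0.08 SD.

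**What adjustment would gain.** Adjusting for baseline multiplies the variance of the cost difference by 1 − rho², and its standard error by the square root of that. The factor does not depend on n.

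| Assumed rho | Variance factor | Variance cut | SE factor | SE cut |
|---|---|---|---|---|
| 0.3 | 0.91 | 9% | 0.95 | 5% |
| 0.5 | 0.75 | 25% | 0.87 | 13% |
| 0.6 | 0.64 | 36% | 0.80 | 20% |

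Put another way, 106 per arm with adjustment would be as precise for costs as 106/0.91 = 116 to 106/0.64 = 166 per arm without it.

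The range of rho is an assumption. Hospital stays and surgery count as costs. If a few such large items dominate and earlier spending predicts them poorly, rho could fall below 0.3 and the gain below 9% of variance.

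**The case against.** **No baseline cost is needed for validity.** Costs that accrue after randomisation can be compared without bias, and chance imbalance is already reflected in the unadjusted standard error. The planned decision analysis does not call for a baseline cost, and the baseline-adjusted ANCOVA lists clinical endpoints only. All of this stands, and it makes the point an improvement in efficiency, not the correction of an error.

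**A reader might infer that economic consent is taken at week 5, after participants know their arm, so that the cost sample is no longer the randomised sample.** The documents do not support this. The sentence on economic consent sets a latest time and no visit. The surrounding text points to early consent: under Design and setting, "Written consent will be obtained from each participant before the start of this trial"; the Randomisation section limits allocation to participants who have consented; and Table 1 places informed consent at visit 1. All that can be said is that the visit for economic consent is not named.

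**A reader might also infer that sites working from Table 1 would not collect costs.** The Economic evaluation section fixes the time points. They coincide with visits 14 and 15, which already exist for both groups, and the missing row contradicts no other statement of timing. The sentence that points to Table 1 closes the section on secondary outcomes, whereas the cost questionnaire is described under Additional analyses. The missing row is a schedule omission; it does not show that data will be lost.

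**Conclusion.** The point holds as a modest improvement to the design of the economic evaluation. The only cost instrument for a stated aim has no measurement before allocation, so the incremental cost cannot be adjusted for earlier resource use or lost workdays.

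The comparison remains unbiased. The loss is in precision: if rho is 0.3 to 0.6, the standard error is larger than it need be, and adjustment would reduce it by 5% to 20%. A typical chance imbalance would shift the incremental cost by about 0.04 to 0.08 SD with no means of correcting it. These figures rest on the assumed correlation, on equal SDs at baseline and follow-up, and on 106 per arm for the imbalance. The primary outcome and its sample size are untouched.

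**What to change.** **Main change.** Add a short cost questionnaire at visit 2 in both arms. It should cover a fixed period before entry and ask about the same resource items and lost workdays as the later forms. It must be completed before the envelope is opened, which fits the existing rule that envelopes stay sealed until all baseline assessments are done. Tie the form to the envelope and not to the visit number alone, because the Randomisation section places allocation at the second visit while Table 1, as it reads in the available copy, marks it under visit 1. Include the visit-2 cost as a covariate in the cost comparison.

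**Housekeeping.** Add a cost questionnaire row to Table 1 at visits 2, 14 and 15 for both groups, and state that consent for economic data is part of the visit-1 informed consent.

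**Cost.** A few minutes per participant at an existing visit, one table row and one line in the consent. No extra visit is needed. If the sponsor prefers not to add the form, the protocol should say that costs will be compared without baseline adjustment.

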### Intervention

#### Moxibustion treatment

Moxibustion treatment will be performed by DKMs who are certified by the Korean Ministry of Health and Welfare. They will have at least 2 years of clinical experience and will have received more than 6 years of oriental medicine college education. The treatment will be performed under the supervision of professors who specialise in acupuncture and moxibustion. All treatment regimens and outcome assessment methods will be standardised between the 4 centres, and basic information about this study and the monitoring process will be disseminated through workshops before the beginning of the study. This study is designed to evaluate moxibustion treatment as it is used in

normal practice. The practitioner will therefore be allowed to maintain a patient-practitioner relationship similar to a normal clinical situation. There will be no restrictions in the careful observation and questioning of participants.

In the moxibustion group, 3 moxibustion sessions per week will be performed during a 4-week period for a total of 12 sessions. The treatment will be conducted after sterilising the skin surface at the acupuncture points with the participant lying in a supine position at a room temperature of 22°C to 28°C. After the top of the moxibustion is sufficiently combusted without attachment to the points for approximately 5 to 10 seconds, the moxibustion will be attached at each point. When a participant believes that their heat tolerance has reached its maximum, the practitioners will place a new moxibustion at the same point. However, to prevent burns, the attached point can be changed to within a 1 cm diameter according to the discretion of the practitioners. A total of 3 moxibustions will be attached at each point at every visit. We will use smokeless indirect moxibustions made of mugwort with a paper cylinder (Manina, Haitnim Co., Korea) (Figure 2). This moxibustion has an adhesive on the bottom that can be used to attach it to the skin, and its effect lasts approximately 5 to 10 minutes. The expected total time of each treatment session will be 20 to 30 minutes. The treatment points were selected in a consensus process by professors and researchers who have an acupuncture and moxibustion specialist license in Korea based on a text book [24], literature reviews [12,14,25],

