### Sample size

We calculated the sample size according to our previous pilot study. A 2-sided 5% significance level and 80% power were considered to detect a mean difference in the WOMAC of -6.65 with a standard deviation (SD) of 15.4. Approximately 84 participants in each group were calculated to be required. Assuming a dropout rate of 20%, the sample size will be  $n = 106$  for each group (total  $n = 212$ ). A total of 32 participants will be assigned at the Korea Institute of Oriental Medicine (Daejeon University Hospital), and the remaining 180 participants will be equally assigned at the other 3 study hospitals. To recruit this number of participants, a 6-month study period is anticipated based on our pilot study.

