### Statistical analysis

The statistical analysis will be performed on the intention-to-treat basis with a 95% confidence interval using SAS (Version 9.1.3; SAS institute Inc., Cary, NC, USA). Missing data will be replaced according to the principle of the last observation carried forward (LOCF) method. The null hypothesis is that there will be no difference in the change in the primary outcome between the moxibustion group and the usual care group after 5 weeks of treatment. The baseline characteristics will be shown as the mean  $\pm$  SD for continuous data (e.g., age and duration of disease) and  $n$  (%) for categorical data (e.g., gender and Kellgren/Lawrence Scale).

To analyse the baseline characteristics, we will perform a 2-sample *t*-test or a Wilcoxon rank sum test for

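### LOCF, the only missing-data rule stated, does not work for costs first recorded at week 5, so the 5-week incremental cost and incremental effect can rest on different participants

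*Protocol*

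**What the plan says.** The protocol's Statistical analysis section states, without exception: "Missing data will be replaced according to the principle of the last observation carried forward (LOCF) method".

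The Economic evaluation section, under Additional analyses, fixes the cost source and timing: "All cost data will be collected through a cost questionnaire that participants" "will complete at 5 weeks and 13 weeks after baseline". The costs counted "will include the direct healthcare-related costs of moxibustion treatment, physician visits, hospital stays", together with drugs and lost workdays. On the horizon it says: "The analysis period will be 5 weeks, and the trend will also be evaluated at 13 weeks". On the method: "The cost-utility and cost-effectiveness analyses will be performed through a decision analysis". The effect measures are quality-adjusted life years from the SF-36 and the K-WOMAC pain subscale.

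Table 1 schedules K-WOMAC and SF-36 at visit 2, week 5 and week 13. It lists no cost questionnaire at baseline. Under Moxibustion treatment, "3 moxibustion sessions per week will be performed during a 4-week period for a total of 12 sessions", so the whole course falls before the week-5 assessment. The Sample size section plans for loss: "Assuming a dropout rate of 20%, the sample size will be" 106 per group.

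**The concern.** LOCF assumes a measured state that can be taken as unchanged until the next visit. A cost is a total over an interval, so carrying it forward has no such meaning. Two situations follow.

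- **Lost before week 5.** No cost has been recorded, so LOCF has nothing to carry. The same person's K-WOMAC pain and SF-36 are scored from visit 2, as no change. The cost half of the ratio then rests on those who reached week 5, and the effect half on everyone randomised.
- **Seen at week 5 but not at week 13.** The only value to carry is the week-5 cost, which contains the moxibustion course. Whatever period the week-13 form covers, that amount is not the missing quantity.

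Cost-effectiveness and cost-utility are part of the second stated aim. The first situation bears on the main 5-week economic analysis, the second on the 13-week trend only.

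**Working it through.** **Inputs from the protocol.** Sample size: difference 6.65, SD 15.4, two-sided 5%, power 80%, dropout 20%, 106 per group. Moxibustion treatment: 12 sessions in 4 weeks. Economic evaluation: costs recorded at weeks 5 and 13 only.

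**The plan's own figure.** n per group = 2 × [15.4 × (1.960 + 0.842) / 6.65]² = 84.2, against about 84 stated. Then 84.2 / 0.8 = 105.2, which rounds up to 106. The figure reproduces. Planned dropouts per group: 0.20 × 106 = 21.2.

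**Participants with no cost to carry.** Let f be the share of dropouts who leave before week 5. The protocol does not give f, so it is shown as a range. The number without any cost is 21.2 × f per group: 0 (f = 0), about 11 (f = 0.5), about 21 (f = 1).

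**Illustrative size at 5 weeks.** Assumptions, none of them in the protocol: dropout is equal by arm, incremental cost is essentially the course (measured in session-costs), those seen at week 5 had 12 sessions and gain effect D, and early dropouts attended a sessions and are scored as no change. Let e be the proportion lost before week 5.

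- Cost from week-5 responders, effect from all randomised: 12 / [(1 − e)D].
- All randomised in both halves: [12(1 − e) + e·a] / [(1 − e)D].

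| e | a | Mixed populations | All randomised in both halves | Excess |
|---|---|---|---|---|
| 0.20 | 4 | 12/0.8 = 15.0 | (9.6 + 0.8)/0.8 = 13.0 | 15% |
| 0.20 | 8 | 15.0 | (9.6 + 1.6)/0.8 = 14.0 | 7% |
| 0.10 | 4 | 12/0.9 = 13.3 | (10.8 + 0.4)/0.9 = 12.4 | 7% |
| 0.10 | 8 | 13.3 | (10.8 + 0.8)/0.9 = 12.9 | 3% |
| 0 | – | 12.0 | 12.0 | 0% |

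Using responders in both halves gives 12 per D, so the mixed ratio at e = 0.20 is 25% higher. That gap comes from LOCF shrinking the effect to 0.8 D, so it does not measure the cost problem. The comparison with the same effect denominator is the 7% to 15%.

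**The 13-week trend.** The late-dropout share is 0.2(1 − f), and the share with any cost value is 1 − 0.2f. The protocol does not say what period the week-13 form covers.

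- *If it covers weeks 6 to 13 only*, carrying week 5 forward repeats the course for late dropouts. Mean course cost is multiplied by [(1 − 0.2f) + 0.2(1 − f)] / (1 − 0.2f): 1.20 (f = 0), 1.11 (f = 0.5), 1.00 (f = 1).
- *If it is cumulative from baseline*, the factor is 1.00 throughout, but all week 6 to 13 costs are dropped for 20%, 11% or 0% of those with a cost value.

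The carried value is wrong on either reading; only the kind of error differs.

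**The case against.** The strongest counter-argument is that LOCF was never meant for costs. The rule stands in the Statistical analysis section, whose listed endpoints do not include costs. The economic evaluation has its own section and method and names no analysis population. On that reading the protocol is merely silent on missing costs, and a method for them may sit in a statistical analysis plan that is not shown.

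This has some force. The protocol does not say whether the rule reaches the economic data, and the imputation model can be left to an analysis plan. But the sentence is unqualified and is the only missing-data rule stated. The mismatch also remains if costs are outside it: LOCF still governs K-WOMAC and SF-36, so early dropouts have an effect score while the only stated cost source holds nothing for them.

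The remaining objections limit the point. A reader might infer that the moxibustion cost is certainly counted twice. The documents do not support that: it depends on the unstated recall period and on LOCF being applied to costs, and it cannot touch the 5-week analysis. A reader might also infer that both problems work against moxibustion and could reverse the economic conclusion. That is not shown either. The analysis takes a social perspective, any other treatment is allowed in both groups, and no unit costs, threshold or dropout timing are given. Other costs could move the ratio in either direction. Finally, the 15% and the factor of 1.20 cannot both occur, since one needs all dropout before week 5 and the other needs all of it after.

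**Conclusion.** The point holds in this form: the one missing-data rule in the protocol does not work for the cost data, and nothing else stated repairs it.

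- **5-week economic analysis.** Between 0 and about 21 participants per group would have an effect score but no cost. Unless corrected, incremental cost and incremental effect would rest on different populations. The illustrative excess is 7% to 15% if all 20% leave before week 5 after 4 to 8 sessions, with equal dropout by arm and a course that dominates incremental cost. It shrinks to nothing as dropout moves later. Otherwise direction and size depend on other costs and on dropout by arm, and cannot be computed from the protocol.
- **13-week trend only.** Carrying the week-5 cost forward is wrong whichever recall period applies.

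This concerns a secondary aim and should be corrected for that aim. It has no bearing on the primary WOMAC analysis.

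**What to change.** Amend the Economic evaluation section as follows.

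1. State that LOCF does not apply to costs, and state the period that the week-13 questionnaire covers.
2. Cost the moxibustion sessions from the treatment record at visits 2 to 13, so that this cost is known for every randomised participant, including dropouts.
3. Treat weeks 1 to 5 and weeks 6 to 13 as separate interval costs, and never carry one into the other.
4. Impute missing costs, SF-36 utility and K-WOMAC pain jointly within arm, for example by multiple imputation using baseline scores, centre, Kellgren/Lawrence grade and sessions attended.
5. Calculate incremental cost and incremental effect on the same randomised population, with a sensitivity analysis using completers in both halves.

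The cost is some wording and a little more analysis work. No extra visits or participants are needed, because sessions are given at visits already scheduled. The small downside is reliance on a missing-at-random assumption; the sensitivity analysis indicates how far the results depend on the imputation.
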